| Evaluate the effect of training on GPs' communication skills and decision support                                             | Percentage of GPs declaring themselves competent in communication on the vaccine     | Self-administered questionnaire                                                                                              | At 2 months, 6 months and 12 months after the intervention |
| 'Facilitation of access to vaccination' component                                                                      |                                                                                      |                                                                                                                              |                                                            |
| Evaluate acceptance of vaccination in middle schools (Secondary Obj. 5)                                                       | Percentage of young people aged 11 to 14 who initiated vaccination in middle schools | Number of doses of vaccine administered in middle school / number of young people eligible for vaccination within the school | Vaccination day                                            |
| Evaluate the satisfaction of teenagers with regard to the intervention (Secondary Obj. 5)                                     | Adolescent satisfaction                                                              | Self-administered questionnaire                                                                                              | After the intervention                                     |
| Evaluate the satisfaction of middle school staff with the intervention (Secondary Obj. 5)                                     | Satisfaction of middle school staff                                                  | Self-administered questionnaire                                                                                              | After the intervention                                     |

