### 5.2. Inclusion and non-inclusion criteria

Inclusion in PrevHPV research is carried out at 2 levels:

- (i) the inclusion of participating municipalities,
- (ii) the inclusion of people participating in the research.

- **Inclusion of participating municipalities:**

The inclusion criteria for municipalities are as follows:

- Municipalities of the academies Aix-Marseille, Clermont-Ferrand, Créteil, Grenoble, Lille, Limoges, Lyon, Nancy-Metz, Nantes, Reims, Strasbourg, Toulouse, Orléans-Tours, Versailles,
- Municipalities in which a total of 1 to 4 middle schools (public or private) are located,

- Municipalities drawn at random from the group of 409 municipalities to be requested to participate in the research,
- Municipalities where all middle schools agree to participate in research.

- **Inclusion of people participating in interventions:**

Inclusion criteria

- ✓ For the intervention component 'Training of GPs' are:

- GPs practicing in the municipalities randomized to groups 1, 2, 5,
- Agreeing to participate in training in motivational interviewing and the use of the decision-aid tool.

**Will not be included:** (i) GPs having exclusively a Particular Mode of Practice, (ii) whose practice within the municipality is planned to stop during the first half of 2021, (iii) GPs with no internet access.

- ✓ For the intervention component 'Education, Motivation, Mobilization', are:

- Adolescents (girls and boys), enrolled in Grades 8 & 9 classes in middle schools (public and private) located in the municipalities randomized to groups 1, 2, 3 and 4,
- Parents of adolescents (girls and boys), enrolled in Grades 6 to 9 classes in middle schools (public and private) located in the municipalities randomized to groups 1, 2, 3 and 4, who agree to participate in an information/education session,

- ✓ For the intervention component 'Facilitation of access to vaccination', are:

- Adolescents (girls and boys), enrolled in middle schools (public and private) located in municipalities randomized to groups 1 and 3, in Grades 6 to 9 classes,
- Aged 11 to 14 on the date of injection, with possible catch-up among 15-19 year olds for those who have repeated a grade, in accordance with the recommendations,
- Not vaccinated against HPV on the date of offer of vaccination in middle school (April - May 2021),
- Whose parents (or representatives of parental authority) agree to the initiation of HPV vaccination in middle school,

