The PrevHPV project managers contact the middle school representatives designated during the “Education, Motivation, Mobilization” intervention and the vaccination center representatives. They agree on the date of vaccination according to the requests and availability of schools and vaccination centers (vaccination can take place over full days or several half-days). They define together the organization to be put in place and the equipment to be made available (various pre-vaccination/post-vaccination letters, familiarization with the equipment available on site: classroom, water point, bed, socket for the computer, table, chairs, emergency kit, catering for the workers if the intervention lasts one day, arrangements for handing over the students, etc.).

The steps of the process are as follows (see flowcharts below):

- (i) In each middle school, the head of the school sends information to parents concerning the presentation of the PrevHPV project (accompanied by the information note specific to the interventions delivered). The middle school referent ensures that information on the vaccination day is disseminated within the school using the most appropriate channels.
- (ii) PrevHPV project managers ensure the distribution of a pre-vaccination letter to schools. A letter containing the main information of the “Facilitation of access” component as well as consent to vaccination is sent to parents through the students, by email and/or made available on the ENT space (e- lyco or Ecole Directe). In this letter, mention is made of the characteristics allowing access to the vaccination offered, carried out by a vaccination center, within the school of the adolescent in question. These characteristics are those presented in the inclusion criteria (see inclusion criteria in the 'Facilitation of access' component, §5.2 Inclusion/non-inclusion criteria). If the adolescent is eligible for vaccination (compliance with all inclusion/non-inclusion criteria), then he or she can benefit from the first injection of the anti-HPV vaccine on the day scheduled at his or her middle school. If in any doubt, parents are encouraged to contact their child's GP or visit the website: <http://vaccination-info-service.fr/>. In the event that parents refuse to vaccinate their child, they can notify in writing directly on the consent document the reason for non-vaccination if they wish.

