- (iii) Parents' consent to their child's vaccination is sent to the school's PrevHPV referent. The PrevHPV referent of the middle school, with the possible help of the PrevHPV project manager of the geographical sector concerned, checks that all consents have been correctly completed (in particular the mandatory presence of the signatures of both parents (except in the event of the death of the parents or of child abandonment) and if necessary, they contact the parents to obtain the missing information. Once the consents for vaccination are complete, the middle school referent establishes the list of adolescents who can benefit from free vaccination within the middle school and keep consents to vaccination within the establishment in a lockable cabinet.

- 1162 (iv) The PrevHPV project manager communicates the number of validated vaccination consents to the  
1163 vaccination center in order to estimate the number of vaccines to order and bring for the vaccination  
1164 day. Consents and the list of adolescents eligible for vaccination are kept at the middle school until  
1165 the team from the vaccination center arrives.
- 1166 (v) The logistical organization of vaccination on the site of each middle school is defined by the  
1167 PrevHPV project managers in partnership with the vaccination centers and the schools. The  
1168 PrevHPV project managers complete the poster informing of the date of the day or half-days of  
1169 vaccination and send it to the schools so that they display it (This poster can be published in A5  
1170 format to be given to adolescents whose parents consent to their vaccination in order to remind them  
1171 of the day of vaccination and the importance of bringing the health/vaccination record). Each school  
1172 teaching staff is also informed of the day scheduled for vaccination.
- 1173 (vi) On the day of vaccination, the vaccination center teams made up of at least: a doctor, a nurse ( $\pm$  the  
1174 PrevHPV project manager) go to the middle schools with the vaccines previously received at the  
1175 vaccination center and their emergency equipment in case of anaphylactic shock. The vaccination  
1176 center team sets up in the provided premises. The students are sent to them according to a  
1177 predefined order of passage in groups of two or three individuals in the room made available to the  
1178 vaccination centers in accordance with the provisions previously established according to the  

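### Acceptance of school vaccination is divided by pupils whose parents have already agreed, so the ratio measures delivery among consented pupils

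*Protocol*

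**What the plan says.** In the protocol's Section 3.2.2, under the component on facilitated access, one row has the objective "Evaluate acceptance of vaccination in middle schools (Secondary Obj. 5"). Its Result column reads "Percentage of young people aged 11 to 14 who initiated vaccination in middle schools". Its measure is "Number of doses of vaccine administered in middle school / number of young people eligible for vaccination within the school", taken on the vaccination day.

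Section 5.2 lists the inclusion criteria for that component. They cover enrolment and age, and they include "Not vaccinated against HPV on the date of offer of vaccination in middle school", "Whose parents (or representatives of parental authority) agree to the initiation of HPV vaccination in middle school", no contraindication and social security affiliation.

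Section 8 uses the same word for pupils. Step (ii) of the vaccination process begins "If the adolescent is eligible for vaccination (compliance with all inclusion/non-inclusion criteria"). Step (iii) says "Once the consents for vaccination are complete, the middle school referent establishes the list of adolescents who can benefit from free vaccination". Step (iv) then says "Consents and the list of adolescents eligible for vaccination are kept at the middle school until" the vaccination team arrives.

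**The concern.** Whether a family accepts the school offer is decided mainly when the parents return, refuse or ignore the consent form. If parental agreement is a condition for entering the denominator, that decision is removed before anything is counted. The ratio then says how many of the pupils with agreement were injected on the day, which is a matter of attendance and organisation.

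The row belongs to secondary objective 5, which looks at levers, barriers and transferability. A figure that does not move with parental agreement cannot show in which schools or settings the offer was taken up. The row also disagrees with itself: the Result column describes a proportion of 11-14 year-olds, with no consent condition, and the measure beside it does not deliver that.

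A smaller mismatch concerns age. Section 5.2 allows catch-up vaccination of some 15-19 year-olds, so doses given at school are not confined to the 11-14 age group named in the Result column.

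**Working it through.** The protocol states no expected value for this outcome, so there is no figure to reproduce. The check has two parts.

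**Tracing the definition**

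1. Section 3.2.2: the denominator is the number of pupils in the school who are eligible for vaccination.
2. Section 8, step (ii): for pupils, eligible means that all inclusion and non-inclusion criteria are met.
3. Section 5.2: parental agreement is one of those criteria.
4. Section 8, steps (iii) and (iv): the list of pupils who can be vaccinated is drawn up from completed consents, and is then called the list of eligible adolescents.

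By these steps, the denominator is the set of consented pupils. On the strictest reading, pupils whose consent is withdrawn or who have a contraindication on the day also fail the criteria and drop out.

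**Arithmetic**

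Inputs:
- N = 466 pupils per school, the mean in Section 11.2, treated there as all aged 11 to 14.
- c = complete consents / enrolled pupils. Not in the protocol; assumed 5% to 30%.
- d = injected / complete consents. Not in the protocol; assumed 0.90 to 0.95.

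Only the first injection is offered at school (Section 8), so doses equal pupils.

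- Ratio as defined = (N × c × d) / (N × c) = d
- Share of enrolled pupils vaccinated at school = (N × c × d) / N = c × d
- First divided by second = 1 / c

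| c | d | Consents | Vaccinated | As defined | Of enrolled | Factor |
|---|---|---|---|---|---|---|
| 5% | 0.90 | 23.3 | 21.0 | 90% | 4.5% | 20 |
| 5% | 0.95 | 23.3 | 22.1 | 95% | 4.75% | 20 |
| 30% | 0.90 | 139.8 | 125.8 | 90% | 27.0% | 3.3 |
| 30% | 0.95 | 139.8 | 132.8 | 95% | 28.5% | 3.3 |

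The consent share c cancels: a school at 5% and a school at 30% score the same for the same d. The level of the ratio is simply the assumed d; with d = 0.80 it would be 80%.

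**Effect of already vaccinated pupils on an all-enrolled denominator**

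Section 11.2 gives a baseline prevalence of 7.86%, so about 466 × (1 − 0.0786) = 429 pupils are unvaccinated. Assume 20% of these have complete consents (85.9) and d = 0.95. Then 85.9 × 0.95 = 81.6 are vaccinated.

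- As defined: 81.6 / 85.9 = 95%
- Of unvaccinated pupils: 81.6 / 429 = 19%
- Of all enrolled pupils: 81.6 / 466 = 17.5%

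At the protocol's own baseline, keeping already vaccinated pupils in costs 1.5 percentage points. Leaving refusing and non-replying families out adds more than 75.

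**The case against.** The best defence is that *eligible* in this row was meant to stop short of consent. Elsewhere the protocol uses the word that way. GPs have their eligibility checked and are then offered the training (Section 5.3), although agreeing is one of their inclusion criteria. Section 8.2.1 calls 2049 municipalities eligible before any school has been asked. The letter described in Section 8, step (ii), reaches parents before they decide, and refusal is then treated as a separate event. With *eligible* read as the right age, unvaccinated and without contraindication, the objective, Result column and measure would broadly agree.

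That may well be what was intended, but those other uses concern GPs and municipalities. For pupils, Section 8 states what the word means and applies it to the consent-based list. Nor could the looser denominator be counted for every family. The footnotes to Section 5.2 have vaccination status checked with parents when authorisation is requested, and contraindications checked at injection, so neither is verified for families who do not reply. Only age is confirmed with the school administration without the parents.

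A second objection stands. A reader might infer that this is the only measure of how families respond, so that a school with few consents would pass unnoticed. The documents do not support that. Section 3.2.1 lists participation of the target population among the criteria for objective 5, Section 10.1 (g) collects it, and Section 11.3.2 (v) plans participation rates. The assessment of the vaccination day in Section 8 counts vaccinations requested, complete and incomplete consents, and vaccinations carried out.

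**Conclusion.** The point holds as one of definition. As written, the acceptance outcome measures delivery among consented pupils, leaves out families who refuse or do not reply, and does not match the Result column of its own row.

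Its size cannot be taken from the protocol. The factor of about 3 to 20 is 1/c under assumed consent of 5% to 30%. A reader might infer that the ratio must come out near 100% by construction. That goes too far: absence, a pupil's own refusal or, unless the criteria are applied strictly, a withdrawn consent or a doctor's decision on the day (Section 7.7) can lower it, and no injection rate is given. What is certain is that the ratio does not depend on the consent share.

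The reach is limited. This is a descriptive outcome for one component. The primary outcome in Section 3.1 uses all adolescents aged 11-14 as its denominator and is untouched. The row should still be corrected, because a published acceptance rate on this definition would be misread.

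**What to change.** In Section 3.2.2, define acceptance as pupils aged 11-14 vaccinated at school divided by all enrolled pupils aged 11-14 in that school, regardless of consent, with age taken at the vaccination day in both. Do not use the word *eligible* for this denominator. Report the two steps beside it, in the same age group: complete consents / enrolled pupils, and vaccinated pupils / complete consents. Catch-up vaccinations at 15-19 can be listed separately.

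This denominator has a drawback: pupils already vaccinated elsewhere count as if they had not accepted, which lowers the figure most where earlier coverage is high. Where prior vaccination status is known, add a version that excludes those pupils, and state that status is not verified for families who do not reply.

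The cost is mainly wording. School size, consent counts and vaccinations carried out are already collected (Sections 8 and 10.1). The extra work is an enrolment count by age from each school and an age split of the consent and vaccination counts. No eligibility criterion or consent procedure changes. The reported acceptance figure will be lower than under the present definition.

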## 4. STUDY DESIGN

### 4.1. Type of research

The PrevHPV trial is a multicenter cluster randomized controlled trial with a 6-arm partial factorial design. The geographical areas covered by the trial correspond to the academies of Aix-Marseille, Clermont-Ferrand, Créteil, Grenoble, Lille, Limoges, Lyon, Nancy-Metz, Nantes, Reims, Strasbourg, Toulouse, Orléans-Tours, and Versailles. These academies were selected to have a diversity of profiles (geographic, behavior/vaccination) across mainland France, in collaboration with the General Directorate of School Education. Within the geographical areas covered by the trial, eligible municipalities are then identified (based on their characteristics and the participation of middle schools in the trial). The cluster, which is the randomization and evaluation unit, correspond to all the inhabitants in a municipality (identified by an administrative code, «code commune»).

The use of a factorial design makes it possible to evaluate the effect of each component of the intervention in isolation (compared to the absence of intervention and between each other), but also the effect of the association of the different components to identify whether it is additive, synergistic or antagonistic.

### 4.2. Research Method

A complete factorial design with 3 factors (= each of the 3 components) results in the constitution of 8 distinct groups. In our case, these 8 groups would be as follows:

- Group 1 benefiting from the 3 components 'Education, Motivation and Mobilization (EMM)' + 'Training of GPs' + 'Facilitation of access to vaccination',
- Group 2 benefiting from 'EMM' + 'Training of GPs',
- Group 3 benefiting from 'EMM' + 'Facilitation of access to vaccination',
- Group 4 benefiting from 'Training of GPs' + 'Facilitation of access to vaccination',
- Group 5 benefiting from 'EMM' only,
- Group 6 benefiting from 'Training of GPs' only,
- Group 7 benefiting from 'Facilitation of access to vaccination' only,
- Group 8 benefiting from none of the 3 components under evaluation (= control group).

However, not all of the above combinations are necessarily relevant. Indeed, it does not seem appropriate to offer vaccination on the school premises (facilitated access) to young people and their parents without them having first benefited from education on HPV infection and its vaccination (EMM), allowing them to make informed decisions. This is the reason why the 'Facilitation of access to vaccination' component will not be implemented without the 'EMM' component, and groups 4 and 7 will therefore not be formed.

Consequently, our partial factorial design will include the following 6 groups:

- **Group 1** benefiting from the 3 components 'Education, Motivation and Mobilization (EMM)' + 'Training of GPs' + 'Facilitation of access to vaccination',
- **Group 2** benefiting from 'EMM' + 'Training of GPs',
- **Group 3** benefiting from 'EMM' + 'Facilitation of access to vaccination',
- **Group 4** benefiting from 'EMM' only,
- **Group 5** benefiting from 'Training of GPs' only,
- **Group 6** benefiting from none of the 3 components evaluated (= control group).

Each group is made up of 15 municipalities (see 11.2 Sample size calculation), making a total of 90 municipalities participating in the PrevHPV trial.

The 'Training of GPs' component of the 45 municipalities in groups 1, 2 and 5 is implemented from December 2020 to April 2021.

The 'EMM' component of the 60 municipalities in groups 1, 2, 3 and 4 is implemented from January to March 2021 and the 'Facilitation of access to vaccination' component of the 30 municipalities of groups 1 and 3 is implemented. work from February to April 2021.

A KABP-6C survey, at the individual level, repeated cross-sectionally (pre and post interventions) will make it possible to answer secondary objective 1 of the PrevHPV trial and thus to assess knowledge, attitudes, beliefs and practices. The KABP-6C questionnaire will be administered to volunteers in the following populations:

- Students, girls and boys, enrolled in Grades Eight and Nine in one of the public or private middle schools in the 90 municipalities of groups 1 to 6 before the implementation of the components in middle schools (December 2020) and after (May 2021).
- Parents, fathers and mothers of girls and/or boys enrolled in Grades Six through Nine in one of the public or private middle schools in the 90 municipalities of groups 1 to 6 before the implementation of the middle school components (December 2020) and after (May 2021).
- GPs practicing regular consultations with adolescents in the 60 municipalities of groups 1, 2, 5 and 6 before the implementation of the component (December 2020) and after (April 2021).

Costs and implementation indicators are collected prospectively by the referent of each middle school with the help of the PrevHPV project manager of the geographical sector concerned, as the different components of the intervention are implemented.

### Randomization groups

|                                                                           | With training of GPs                                                                                             | Without training of GPs                                     |
|---------------------------------------------------------------------------|------------------------------------------------------------------------------------------------------------------|-------------------------------------------------------------|
| Education, motivation, mobilization                                | Education, motivation, mobilization
+ Training of GPs                                                         | Education, motivation, mobilization only             |
| Education, motivation, mobilization + Facilitation of access       | Education, motivation, mobilization
+ Facilitated access
+ Training of GPs
Complete intervention | Education, motivation, mobilization
+ Facilitated access |
| No Education, motivation, mobilization + No Facilitation of access | Training of GPs only                                                                                      | No intervention                                      |

